## Abstract

**Background:**

Metastatic disease in tumors originating from the gastrointestinal tract can exhibit varying degrees of tumor burden at presentation. Some patients follow a less aggressive disease course, characterized by a limited number of metastatic sites, referred to as “oligo-metastatic disease” (OMD). The precise biological characteristics that define the oligometastatic behavior remain uncertain. In this study, we present a protocol designed to prospectively identify OMD, with the aim of proposing novel therapeutic approaches and monitoring strategies.

**Methods:**

The PREDICTION study is a monocentric, prospective, observational investigation. Enrolled patients will receive standard treatment, while translational activities will involve analysis of the tumor microenvironment and genomic profiling using immunohistochemistry and next-generation sequencing, respectively. The first primary objective (descriptive) is to determine the prevalence of biological characteristics in OMD derived from gastrointestinal tract neoplasms, including high genetic concordance between primary tumors and metastases, a significant infiltration of T lymphocytes, and the absence of clonal evolution favoring specific driver genes (*KRAS* and *PIK3CA*). The second co-primary objective (analytic) is to identify a prognostic score for true OMD, with a primary focus on metastatic colorectal cancer. The score will comprise genetic concordance (> 80%), high T-lymphocyte infiltration, and the absence of clonal evolution favoring driver genes. It is hypothesized that patients with true OMD (score 3+) will have a lower rate of progression/recurrence within one year (20%) compared to those with false OMD (80%). The endpoint of the co-primary objective is the rate of recurrence/progression at one year. Considering a reasonable probability (60%) of the three factors occurring simultaneously in true OMD (score 3+), using a significance level of α = 0.05 and a test power of 90%, the study requires a minimum enrollment of 32 patients.

**Discussion:**

Few studies have explored the precise genetic and biological features of OMD thus far. In clinical settings, the diagnosis of OMD is typically made retrospectively, as some patients who undergo intensive treatment for oligometastases develop polymetastatic diseases within a year, while others do not experience disease progression (true OMD). In the coming years, the identification of true OMD will allow us to employ more personalized and comprehensive strategies in cancer treatment.

**Trial registration:**

ClinicalTrials.gov ID NCT05806151.

## Background

Cancer spreading to distant organs, such as the lungs, liver, bones, and brain from primary tumors, remains the primary cause of cancer-related deaths. The extent of cancer spread is commonly assessed by factors including the number, size, and involvement of loco-regional lymph nodes, which are then used to guide clinical staging systems [1, 2]. However, metastatic disease in stage IV cancers can present with widely varying initial tumor burdens [3]. Patients may present with a highly metastatic pattern involving multiple sites, known as “poly-metastatic disease” (PMD), or with a less severe disease course involving fewer sites, referred to as “oligo-metastatic disease” (OMD) [4]. OMD manifests in 2–10% of patients across diverse cancer types, depending on the specific histological subtype. The term OMD is applied when the disease presents with no more than three lesions per organ and a total maximum size equal to 7 cm [5], or a primary tumor (active or resected) with ≤ 5 easily resectable lesions (with a size limit of 5 cm) [6], or controllable metastatic masses amenable to local approaches [7]. Oligo-metastatic patients generally have a favorable prognosis because the disease has a prolonged course that can be effectively controlled with local treatments (such as radiotherapy or radiofrequency ablation) and less aggressive systemic therapies. OMD is not merely an intermediate stage between localized, low-burden disease and diffuse metastases; it represents a distinct disease entity with specific biological and molecular features. The low “metastatic virulence” observed in OMD may reflect specific and dynamic aspects of tumor biology and/or host-tumor relationships [8]. Guckenberger et al. [9] interestingly redefined OMD in oncology as “induced” OMD (occurring in patients with a history of poly-metastatic cancer prior to the diagnosis of OMD) and “de novo” OMD (in patients without a history of poly-metastatic disease prior to the diagnosis of OMD), with the latter group having a favorable prognosis. However, the biological characteristics that uniquely identify oligometastatic behavior remain unknown, and the definition of a ‘true’ and good-prognosis OMD is necessarily retrospective, as many patients initially classified as oligometastatic eventually develop polymetastatic disease (PMD) within one year.

### Rationale

We have previously presented evidence regarding OMD in colorectal cancer [10–12]. Patients diagnosed with oligometastatic colorectal carcinoma generally exhibit a notably enhanced median survival rate, approximately 44.0 months, in comparison to those with PMD, where the median survival is 24.0 months [13]. Moreover, in two earlier studies, we established substantial genetic and immunological distinctions between OMD and PMD. Notably, we observed an elevated occurrence of the *ERBB2* p.Pro1170Ala variant in oligometastatic lung disease [14], and an absence of *PIK3CA* mutations in oligometastatic liver and lung disease [15]. Among the patients with OMD, 9 out of 11 (81.8%) showed reversion in *KRAS* mutation at metastatic sites, whereas only 1 out of 52 (1.9%) with progressive PMD exhibited *KRAS* mutation reversal, with the majority acquiring *KRAS* mutations [16]. Consistently, tumor DNA sequencing results revealed a high level of genetic concordance in patients with OMD, with genetic coding variants showing over 80% concordance between the primary tumor and corresponding oligo-metastases [10–12, 14, 15]. Additionally, we observed an increased infiltration of GRZB + lymphocytes, which are activated cytotoxic lymphocytes, in oligometastatic liver disease with a favorable prognosis, indicating complex immunological interactions within the tumor microenvironment [14, 15]. The primary objective of the PREDICTION study is to identify OMD from a biological and molecular perspective, aiming to propose innovative therapeutic and monitoring strategies.

### Study design

The PREDICTION study is a prospective, observational, and monocentric investigation. Patients enrolled in the study will receive standard treatment. Translational activities will include the analysis of the tumor microenvironment in all accessible lesions, as well as genomic profiling of samples from enrolled patients to assess genetic concordance between primary and metastatic tumors, and to examine the mutational evolution of key driver genes.

### Study population

The study population consists of patients affected by gastroenteric cancers (colon, stomach, biliary tract, exocrine glands of the digestive tract) with OMD. Oligometastatic patients present one to three lesions per organ with a maximum tumor diameter of less than 70 mm and no lesion with a diameter greater than 25 mm. The correct identification of oligometastatic patients for the study will be performed through radiological staging techniques such as Computed Tomography (CT) and/or Magnetic Resonance Imaging (MRI). It is important to differentiate between two clinical presentations in OMD: those presenting with “oligo-recurrence” and those with “sync-oligometastatic” cases [17–19]. In the former, the primary tumor has been effectively controlled through a radical local approach, while in the latter, oligo-metastatic disease manifests synchronously with an active primary tumor. The PREDICTION study will include patients with both presentation types, contingent upon their having undergone radical treatment for all lesions.

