### Secondary objectives

To describe the types of treatments received by patients with oligo-metastatic colon-rectal cancer;To measure the response evaluated according to Response Evaluation Criteria in Solid Tumors (RECIST) version 1.1;To measure the duration of the response, from the time the objective response is documented until progression;To evaluate progression-free survival (PFS) and overall survival (OS).To describe genetic and immunologic differences between “oligo-recurrence” and “sync-oligo-metastatic” cases.

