### Study design and statistical analyses

The study aims to achieve its analytical/prognostic objective by enrolling a sufficient number of patients to demonstrate that “true” oligometastatic CRC (score 3+) have a significantly lower progression rate (defined as recurrence after radical surgery or progression according to RECIST v 1.1 criteria from the time of enrolment in the study) within 1 year compared to those with “false” OMD (score < 3+). The primary endpoint will be recurrence/progression within 1 year.

The sample size was determined using a two-sided test of difference between proportions to evaluate the statistical significance of the difference in recurrence within 1 year.

For this purpose, the following scenario was considered:

A reasonable probability of the simultaneous occurrence of the 3 factors in true OMD (score 3+) of 60% [14, 15, 19];A recurrence rate of 20% for true OMD (score 3+) [11], and 80% for false OMD (score < 3+) [10–15, 19].

With a significance level of α = 0.05, a test power of 90%, and a Fisher exact test, the required number of patients to be enrolled is 32, to be recruited over an expected period of 3 years.

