### Screening procedures

The screening phase of the study will involve the evaluation of both inclusion and exclusion criteria. If deemed eligible, patients will be provided with information about the study objectives, treatment options determined by the oncologist following standard clinical practice, the necessity of conducting analyses on tissue samples collected during their treatment history, or in cases where metastatic tissue samples are unavailable, molecular characterization via liquid biopsy. Patients will also be informed about the procedures involved and the potential associated risks. To participate in the study, patients will be required to sign a specific informed consent form. The timing of study procedures is summarized in Table 1.

**Table 1 Tab1:** Study procedures

Study assessments	Screening phase	Enrolment	At oligo-metastases treatment	Every 3 months	End of study	Follow-up
Informed consent	X					
Eligibility	X					
Pregnancy test	X					
Anamnesis	X					
Concurrent medications	X			X	X	X
Cardiologic evaluation	X			X		X
Height	X					
Weight	X			X	X	X
Clinical examination, ECOG PS, vital signs	X			X	X	X
Blood count and clinical biochemistry, CEA and CA19.9		X		X	X	X
Urinalysis		X			X	X
Creatinine clearance		X			X	X
Assessment of angiogenic factors		X				
Characterization of the tumor microenvironment of primary tumor		X				
Characterization of the tumor microenvironment of metastasis			X*			
Genetic assessment of the primary tumor		X				
Genetic assessment of the metastasis			X*			
Liquid biopsy			X**			
Total-body computed tomography with i.v. contrast (if contraindicated: abdomen MRI and chest computed tomography without i.v. contrast)	X			X	X	X
Adverse events evaluation				X	X	X
Progression				X	X	X
Survival				X	X	X

*After Surgical Treatment

**Oligo-metastatic patients not eligible for an upfront loco-regional treatment

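### Inclusion depends on radical treatment that Table 1 places after enrolment, while the one-year endpoint runs from enrolment; read literally, early progressors are removed because of their outcome

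*Protocol article*

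**What the plan says.** **Population.** The Study population section takes both oligo-recurrent and synchronous presentations, "contingent upon their having undergone radical treatment for all lesions". The Inclusion criteria require tumour type, lesion number and size, archived tissue from the resected primary, and consent. They do not mention radical treatment of all lesions.

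**Sequence.** Table 1 (Screening procedures) has separate columns for enrolment and, after it, treatment of the oligometastases. Genetic and microenvironment assessment of the metastasis stand in the later column, footnoted "After Surgical Treatment". Liquid biopsy stands in the same column, for "Oligo-metastatic patients not eligible for an upfront loco-regional treatment". The Fig. 2 caption also covers lesions unsuitable for upfront surgical removal.

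**Clock.** Primary objectives, Study design and statistical analyses, and Follow-up procedures all time recurrence or RECIST progression from enrolment; the second of these reads "from the time of enrolment in the study".

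**Score.** Two of the three points (primary/metastasis concordance, and absence of *KRAS*/*PIK3CA* mutations in metastases) need molecular information on the metastasis. The GRZB point can be scored on the primary alone.

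**The concern.** The population statement and the endpoint definition give opposite answers for the same patient. Someone enrolled with oligometastases who progresses before all lesions are radically treated has had a co-primary event by the endpoint definition. By the population statement that patient never qualified. No section says which rule prevails.

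If the population statement prevails, membership of the analysis set depends on something that happens after time zero and that progression itself can prevent. Under the trial's own hypothesis, early progressors are mainly false OMD, so the loss is unequal. It thins the smaller group, lowers both observed one-year rates and raises the apparent proportion with score 3+. The comparison at stake is the only one that was powered. The same condition governs the population for the prevalence objective.

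**Working it through.** **Inputs.** From Study design and statistical analyses: 20% against 80% at one year, 60% with score 3+, two-sided ("The sample size was determined using a two-sided test of difference between proportions"), α = 0.05, "a test power of 90%, and a Fisher exact test", N = 32. The documents give no time from enrolment to treatment, so the lag L is an assumption and is shown as a range.

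**1. The plan's own figure.** A 60:40 split of 32 is about 19 and 13. Full enumeration of the two-sided Fisher test gives power 92.7%. With N = 31 (19 and 12) it is 89.4%, so 32 is the smallest total reaching 90%. The sample-size arithmetic is sound.

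**2. Model.** Constant hazards from enrolment, matched to the planned rates:

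- true OMD: h = −ln(0.8)/12 = 0.0186 per month
- false OMD: h = −ln(0.2)/12 = 0.1341 per month

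All patients share one lag L, and those who progress before L are removed.

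- Lost before treatment: 1 − exp(−hL)
- Observed rate among those left, with the year still counted from enrolment: 1 − exp(−h(12 − L))
- Patients left: 19 or 13 × exp(−hL)

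Example at L = 3:

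- Lost: 1 − exp(−0.0558) = 5.4% of true and 1 − exp(−0.4024) = 33.1% of false OMD.
- Left: 19 × 0.946 = 18.0 and 13 × 0.669 = 8.7.
- Score-3+ share: 18.0/(18.0 + 8.7) = 67%, against 19/32 = 59% at enrolment.

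**3. Results.** Exact Fisher power, group sizes rounded:

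| Lag (months) | Lost, true / false | Observed rates | Patients left | Score-3+ share | Power |
|---|---|---|---|---|---|
| 0 | 0% / 0% | 20.0% / 80.0% | 19 / 13 | 59% | 92.7% |
| 1 | 1.8% / 12.6% | 18.5% / 77.1% | 19 / 11 | 62% | 88% |
| 3 | 5.4% / 33.1% | 15.4% / 70.1% | 18 / 9 | 67% | 79% |
| 6 | 10.6% / 55.3% | 10.6% / 55.3% | 17 / 6 | 75% | 55% |

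**4. Contrast.** If the same patients are kept and their progression is counted from enrolment, the rates stay at 20% and 80% with 19 and 13 patients. Nothing is lost. The whole effect in the table comes from the exclusion.

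**The case against.** The strongest reply is that the endpoint definition already handles these patients. RECIST progression counts from enrolment, so progression before surgery is an event. Nor is an unresected patient necessarily unscorable: Screening procedures and the sequencing methods provide liquid biopsy where metastatic tissue is lacking, and GRZB can be read on the primary. On that reading nobody drops out. This stands as an account of what the endpoint and sampling sections allow, and it shows that the repair needs little new machinery. It does not remove the condition in the Study population section, which still excludes the patients whom the other sections would score and count.

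A second reply is that the condition may mean treatment completed before enrolment, and that some metastatic tissue may come from the treatment history. Figs. 1 and 2, which illustrate the timing, are not available here. This is possible for some patients. As a general reading it conflicts with Table 1, where treatment of the oligometastases follows enrolment.

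Third, the size of the effect rests on assumed lags common to all patients, and at one month it is modest. That is correct. The contradiction does not depend on the lag, but the loss of power does.

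**Conclusion.** The population condition is wrong as written. It contradicts the inclusion criteria, the schedule and the endpoint's time zero, and applied literally it removes patients because of their outcome. The loss falls mainly on false OMD. Under the stated assumptions, power drops from 92.7% to between about 88% (1-month lag) and 55% (6 months), and the score-3+ share rises from 59% to between 62% and 75%. These figures illustrate the risk. The exclusion is inferred from reading the sections together and is not an announced rule, and the real lag is unknown.

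A reader might infer more than the documents support:

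- **Immortal time bias favouring score 3+.** Both score groups pass through the same sampling step. Neither is credited by design with event-free time that the other lacks.
- **Power lost merely because post-surgical risk time is shorter.** With 4- or 6-month lags for everyone and no events before surgery, power would be 86% or 78%. But the endpoint counts pre-surgical progression, and even that model gives 91.5% at 1 month and 90.0% at 2 months.
- **The clock must start at completed local treatment.** That choice would itself leave early progressors without a time zero.
- **Response and its duration cannot be measured.** The secondary objective "To measure the duration of the response, from the time the objective response is documented until progression" would fail only if every lesion were treated before enrolment, which Table 1 does not indicate.

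**What to change.** Reconcile Study population, Primary objectives, Study design and statistical analyses, Inclusion criteria and Table 1, so that the co-primary set does not depend on an event after enrolment:

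1. Drop the radical-treatment condition for the co-primary analysis.
2. Keep enrolment as time zero and analyse all enrolled colorectal patients.
3. State that progression before radical treatment is an event.
4. Score unresected patients by the route already provided: plasma for the metastatic genetics and the primary tumour for GRZB. Table 1 ties the plasma sample to the treatment step, so it should also say how patients who progress before that step are sampled.
5. As a sensitivity analysis, report the one-year rate, and PFS and OS by score, from a landmark at which local treatment is complete and the score determinable. Tabulate the patients who never reach it, with their outcomes.

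The cost is small: a change of wording, one extra analysis, and some patients scored on plasma instead of tissue. The two assays have different detection limits (0.1% for plasma, 5% for tissue), so the source of each score should be reported.

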### Primary objectives

This study has two main objectives. The first objective aims to determine the prevalence of specific biological characteristics in OMD arising from gastrointestinal tract neoplasms, including those in the colon, stomach, biliary tract, and exocrine glands of the digestive tract. These biological characteristics encompass: (1) high genetic concordance between primary tumors and metastases, (2) the presence of a high T lymphocyte infiltrate in the primary tumor and/or metastases, and (3) the absence of clonal evolution that favours specific driver genes. The primary endpoint of the first objective is to delineate the prevalence of these biological characteristics. Our center has the potential to annually recruit 11 new oligometastatic patients with colon tumors, 5 with stomach tumors, 3 with biliary tract tumors, and 3 with exocrine gland tumors of the digestive tract suffering from these pathologies.

The second co-primary objective aims to identify a prognostic score that identify true OMD. This score is tested in a single pathology, namely patients with metastatic colorectal cancer, which is the most common gastroenteric cancer associated with OMD. The score is based on the following characteristics, and possession of all characteristics (3+) constitutes the full score:

Primitive/metastasis genetic concordance > 80% = 1 point;High T-lymphocyte infiltration - GRZB+ (> 10 cells/mm2) in the primary tumor and/or metastases (where tissue is available) = 1 point;Absence of clonal evolution favouring specific driver genes [absence of *KRAS* and/or *PIK3CA* mutations in metastases, even with a mutated primary (i.e., clonal evolution not favoring metastases)] = 1 point.

The hypothesis is that patients with true OMD (score 3+) have a significantly lower rate of progression at one year, defined as recurrence after radical surgery or progression based on RECIST v 1.1 criteria [20] since enrolment in the study, compared to those with false OMD who subsequently develop PMD. The primary endpoint for this objective is the rate of recurrence/progression within one year.

### Secondary objectives

To describe the types of treatments received by patients with oligo-metastatic colon-rectal cancer;To measure the response evaluated according to Response Evaluation Criteria in Solid Tumors (RECIST) version 1.1;To measure the duration of the response, from the time the objective response is documented until progression;To evaluate progression-free survival (PFS) and overall survival (OS).To describe genetic and immunologic differences between “oligo-recurrence” and “sync-oligo-metastatic” cases.

### Study design and statistical analyses

The study aims to achieve its analytical/prognostic objective by enrolling a sufficient number of patients to demonstrate that “true” oligometastatic CRC (score 3+) have a significantly lower progression rate (defined as recurrence after radical surgery or progression according to RECIST v 1.1 criteria from the time of enrolment in the study) within 1 year compared to those with “false” OMD (score < 3+). The primary endpoint will be recurrence/progression within 1 year.

The sample size was determined using a two-sided test of difference between proportions to evaluate the statistical significance of the difference in recurrence within 1 year.

For this purpose, the following scenario was considered:

A reasonable probability of the simultaneous occurrence of the 3 factors in true OMD (score 3+) of 60% [14, 15, 19];A recurrence rate of 20% for true OMD (score 3+) [11], and 80% for false OMD (score < 3+) [10–15, 19].

With a significance level of α = 0.05, a test power of 90%, and a Fisher exact test, the required number of patients to be enrolled is 32, to be recruited over an expected period of 3 years.

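### The 32 patients are correctly derived but are the exact minimum of evaluable colorectal patients, printed as an enrolment figure with almost no room for losses

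*Protocol article*

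**What the plan says.** Study design and statistical analyses sizes the co-primary comparison of one-year recurrence or progression between colorectal patients with the full score and those below it. The rates are 20% and 80%, and 60% of patients are expected to reach the full score. "The sample size was determined using a two-sided test of difference between proportions"; the error rate is set at 5%, the power at 90%, and Fisher's test is named. The section then gives its result: "the required number of patients to be enrolled is 32, to be recruited over an expected period of 3 years". The abstract gives the same number as "the study requires a minimum enrollment of 32 patients".

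Primary objectives restricts the score test to colorectal cancer, while the study enrols four tumour groups. On capacity it says "Our center has the potential to annually recruit 11 new oligometastatic patients with colon tumors", plus 5 stomach, 3 biliary and 3 exocrine gland patients a year.

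On sampling, Screening procedures provides, "in cases where metastatic tissue samples are unavailable, molecular characterization via liquid biopsy". In Table 1 of the same section, metastatic tissue is characterised after surgical treatment, and the liquid biopsy row is footnoted "Oligo-metastatic patients not eligible for an upfront loco-regional treatment".

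Ethical considerations states that a withdrawn patient's data are left out of any analysis not already completed.

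**The concern.** A power calculation returns the number of patients who enter the test. Here each of them needs a complete score, including metastatic genetics, and a known 12-month status. The protocol prints that number as the number to enrol and adds nothing for patients who drop out of the analysis, although its own rules foresee such patients. If 32 is the exact minimum, every loss comes out of the stated power. The label also omits that the number concerns colorectal patients only. What is at stake is whether the co-primary comparison keeps roughly the 90% claimed, and whether a reader can tell how many patients of which kind are needed.

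**Working it through.** **Inputs** (Study design and statistical analyses): p1 = 0.20 with the full score, p2 = 0.80 below it, 60:40 split, two-sided α = 0.05, Fisher's exact test, target power 90%.

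**Method.** For group sizes n1 and n2, power is the sum, over all tables (x, y) whose two-sided Fisher p-value is at most 0.05, of Bin(x; n1, 0.20) × Bin(y; n2, 0.80). Score status is observed and not allocated, so the more relevant figure averages this over n1 ~ Binomial(N, 0.6).

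**Step 1: reproduce 32.** At N = 32 the 60:40 split rounds to 19:13. Power is 92.7% at that split and 90.8% averaged. At N = 31 it is 89.4% at the rounded split (19:12) and 89.8% averaged. So 32 is confirmed as the smallest total reaching 90% by either calculation, with no reserve.

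**Step 2: one loss.** From 19:13, losing a patient below the full score gives 19:12 and 89.4%. Losing a full-score patient gives 18:13 and 90.9%. The shortfall is at most 0.6 points, and there may be none.

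**Step 3: several losses.** The documents give no loss rate, so 10% and 20% are assumptions: 32 × 0.9 = 28.8, about 29; 32 × 0.8 = 25.6, about 26. Averaged power for Fisher, and for Boschloo's unconditional exact test (Fisher's p-value as the statistic, two-sided 0.05):

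| Evaluable | Fisher | Boschloo |
|---|---|---|
| 32 | 90.8% | 93.4% |
| 30 | 88.2% | 92.1% |
| 29 (10% loss) | 87.7% | 90.8% |
| 28 | 84.9% | 89.6% |
| 26 (20% loss) | 84.3% | 87.4% |

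**Step 4: accrual.** 11 colon patients a year × 3 years = 33, and 33 − 32 = 1. Enrolling enough for 32 evaluable would take 32/0.95 → 34, 32/0.90 → 36 or 32/0.80 → 40 patients. All exceed 33.

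**Step 5: who can be scored.** Genetic concordance and absence of driver-gene evolution both need metastatic genetic material. The T-cell item can be read from the primary tumour, whose tissue is an inclusion criterion. The sources for metastatic genetics are:

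- Screening procedures: plasma when metastatic tissue is unavailable.
- Next-generation sequencing: plasma when tissue is insufficient or inadequate.
- Fig. 2 legend: plasma for lesions not suited to upfront surgery.
- Table 1: tissue after surgery; plasma only for patients who cannot have upfront loco-regional treatment.

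A patient given upfront local treatment other than surgery is covered by the first statement but has neither sample under Table 1. The Background names radiotherapy and radiofrequency ablation among local treatments for oligometastatic disease, so the case is not remote. Followed literally, Table 1 leaves that patient without two of the three items.

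**The case against.** The strongest reply is that nothing is miscalculated: 32 is correct, Fisher is valid, and the planned test matches the one used for sizing. That stands.

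It can also be said that losses are partly addressed. Inability to guarantee follow-up is an exclusion criterion, non-progressors are followed for at least a year, and the handling of unevaluable patients is commonly left to a full protocol or analysis plan not shown here. This stands for the handling rules. It does not cover a number that the article itself fixes and labels as enrolment.

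Three statements allow plasma more widely than the Table 1 footnote, so the footnote may simply be compressed. That is plausible. The mismatch does not prove that a class of patients will go unscored, but it decides who can be scored and has to be resolved.

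A reader might infer from the abstract that 32 is the total over all four tumour groups, so that only about half (11 of 22 a year) would enter the test. The documents do not support this. The methods section names colorectal cancer as the comparison being sized, and in the abstract 32 closes the description of the co-primary objective and is called a minimum. Three years at 11 a year gives 33, whereas 22 a year over all types would reach 32 in about 1.5 years.

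**Conclusion.** The concern holds as a matter of labelling, margin and one internal inconsistency; there is no arithmetic error. The figure 32 is the smallest evaluable colorectal number reaching 90% under the stated inputs, is presented as enrolment, and sits one below the projected 3-year supply.

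The effect is moderate. Averaged power falls from 90.8% to 87.7% with an assumed 10% loss and to 84.3% with an assumed 20% loss. It would be wrong to conclude that the stated power collapses with a single unusable patient, since one loss leaves 89.4% to 90.9%. These figures take the 20%, 80% and 60:40 assumptions as given and treat losses as unrelated to score and outcome. This is an inexpensive clarification worth making; it does not invalidate the design.

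**What to change.** 1. Restate the figure in both the abstract and the methods section as 32 evaluable colorectal patients, meaning score and 12-month status both known. Report expected numbers for the other tumour groups separately, under the descriptive objective.
2. State the power at 26 to 31 evaluable patients, with the loss rate labelled as an assumption. The alternative is to enrol 34 to 40 for an assumed 5% to 20% loss, but at 11 colon patients a year that runs past the planned 3 years (36/11 ≈ 3.3 years).
3. Reconcile the Table 1 liquid biopsy footnote with Screening procedures, Next-generation sequencing and the Fig. 2 legend, so that it is clear which patients have a source for metastatic genetics.
4. As an improvement and not a correction, prespecify Boschloo's unconditional exact test for the co-primary comparison. Its size is at most 5%, and it is never less powerful than Fisher because it rejects whenever Fisher does. Averaged power is 93.4% at 32, 90.8% at 29 and 87.4% at 26.

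Items 1 and 3 are wording, and item 2, as power reporting, adds a few figures. Item 4 costs a less familiar test and slightly more computation. None of these needs extra patients unless the larger enrolment in item 2 is chosen. The price of openness is that the stated power looks a little less favourable once losses are shown.
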